### Interventions

#### Phase 1

##### Iterative design

Women (*N* = 10) will be asked to come to the Healthy Lifestyles Research Lab at a *University in the Southwestern United States* for nine sessions (i.e., 20–60 min)*.* Thirty online yoga videos from Udaya’s library, preselected by a yoga therapist and the principal investigator, will be randomly assigned (using a random number table) to participants. Each participant will be randomly assigned nine different online yoga videos so that each video is reviewed at least three times. Selection criteria for the 30 online yoga videos include the following: (1) have been used in our previous beta-testing [51] *and were* positively reviewed by mothers bereaved by stillbirth, (2) videos that the research team believes will cultivate emotional regulation and self-compassion (evidence-based proposed mediators from a general population with PTSD), (3) classes that are slower moving (i.e., beginner-based) with detailed instruction and alignment cues (i.e., safe and proper form), and (4) classes that are safe for women up to 20 weeks gestation in case a woman becomes pregnant during the intervention. Each woman will be asked to watch/engage in the yoga video by herself in an observation room. Participants will not be able to review more than one video per day to limit influence from another video. Before and after engaging in the yoga videos, women will be asked two investigator-developed questions related to the potential mechanisms by which yoga may reduce PTSD symptoms, including self-compassion [How much self-compassion do you feel (i.e., self-kindness, understanding toward yourself and your grief, common humanity, mindfulness) right now?] and emotional regulation [How much do you feel that you are able to be with your emotions (i.e., consciously stay with your emotions or mood) right now?]. Questions will be answered on a five-point Likert scale. Mean scores will be taken for each video and entered into an Excel document. Those videos that elicit the *highest* self-compassion and/or emotional regulation will *be used for phase 2*.

### Interviews

One research staff member trained by an expert in qualitative research will conduct the interviews using a semi-structured interview guide. All interviews (*N* = 5) will be recorded and transcribed verbatim. The insight provided from the interviews will be used to modify the recruitment materials for phase 2 as needed.

#### Phase 2

The online videos prescribed in all three conditions will be suitable for women up to 20 weeks gestation (the maximum possible based on our study eligibility) in the case that a participant becomes pregnant during the study. Additionally, a nationally certified instructor (i.e., yoga or fitness) will teach the online videos.

##### Low and moderate dose intervention groups

The low and moderate dose intervention groups will be asked to follow a 12-week online yoga prescription (for 60 and 150 min/week, respectively). We selected the low dose of 60 min/week because this is the minimal amount needed to experience mental and/or physical health benefits [40, 52–55]. We chose the moderate dose of 150 min/week because this reflects the physical activity guidelines [56].

The style of the online yoga videos will be Hatha because (1) Hatha combines a physical practice with a meditative component to cultivate mindfulness (i.e., moment to moment, non-judgmental awareness, cultivated by paying attention in a specific way) [57] and self-awareness and (2) includes instruction from a variety of lineages (e.g., Iyengar, Asthanga, Vinyasa). The online prescription assures the poses used are identical for both intervention groups. Participants will be asked to complete the yoga videos in a specific order, which will include specialized preparatory instructions for each video to ensure comfort and safety [56].

##### Stretch and tone control group

The STC group will be asked to follow a 12-week online stretching/toning exercise prescription for 60 min/week to match minimal dose of intervention group (i.e., LD). We will develop 12, 30-min videos for the STC group prescription (produced and filmed by UDAYA). The STC videos will be adapted from an already existing, well-established, evidence-based control condition (originally designed for older adults in other funded trials) to be specific for women who are underactive (<150 min of moderate activity per week) [47–49, 58, 59]. The instructor will begin and end each class with a 3-min warm-up/cooldown. The instructor will ask participants to perform each isolated stretch or toning exercise for 1–2 sets (20–45 s or between 10 and 15 repetitions). Participants will be asked to perform slow, controlled, and complete movements. Progression will include demonstration by the instructor of modifications with a slightly less difficult and a more challenging version for the specific exercise. For example, a participant may be asked to perform a plank on their knees and a modification may be to straighten their legs, making the exercise more difficult. Variability will be demonstrated by changing the stretching and toning exercises every 3 weeks. For example, in the first 3 weeks, participants will be introduced to the new activities, and in the remaining weeks 4 to 12, they are encouraged to increase the difficulty by adding more repetition or performing the more challenging modification. Participants will be asked to complete the STC videos in a specific order, which will include a warm-up, four upper body, four lower body, three trunk/core, and one to two balance exercises, with appropriate progression over 12 weeks. The STC videos will have discussion related to form and safety by the instructor (i.e., no guidance for movement with breath or mindfulness). Additionally, videos will have students in the background following instructor cues and demonstrating variations of exercises. There will be no final relaxation pose in the STC videos (i.e., the rest period after completion of a yoga class).

##### Procedures

UDAYA will provide the research team with 90 membership accounts pre-paid for the length of the study that will have access only to the videos specific to the participants group assignment (i.e., participants will not have access to the full UDAYA video library). The research staff will assign UDAYA membership accounts to all participants (i.e., intervention and control) upon enrollment into the study and will provide them with a username and password to access UDAYA prior to their participation in the study. In addition, participants will be asked to wear an accelerometer (i.e., GENEActiv) to measure physical activity and sleep quality for 1 week at baseline, post-intervention (12 weeks from baseline), and follow-up (20 weeks from baseline) and complete assessments at these time points.

Participation in the videos (intervention and control groups) will be automatically tracked (class taken, time of day, length of use, and etc.) via web analytics software throughout the study in each group. Research personnel will send weekly reminders (email or text message) to participants for minimal dose compliance. Additionally, the research team will send each participant a Qualtrics link to report (1) completion of sessions, (2) rating of perceived exertion, (3) assessment of mindfulness, (4) other physical activity participation, (5) pregnancy status, mental health, use of psychiatric medication, and adverse events. Participants will be asked weekly about participation in support groups or individual/group-based counseling sessions. Participants will be discouraged from attending face-to-face yoga/stretching/toning classes during the study.

In the case that a woman becomes pregnant during the study, she will be asked to complete the Physical Activity Readiness Medical Examination for Pregnancy (PARmed-X for Pregnancy), a health screening tool completed with the health care provider to ensure it is safe for women to participate in prenatal exercise. We will also send women a pregnancy safety handout (specific to yoga or general physical activity depending on group assignment) for their review.

The study will be stopped prior to its completion based upon (1) clinical deterioration of PTSD symptomology (increased scores of >20 points from baseline on the Impact of Event Scale-Revised (IES-R) in >50% of the enrolled participants), (2) difficulty in study recruitment (i.e., at halfway through the timeline of recruitment, study recruitment falls below 30% of the total recruitment goal), and (3) if any new safety information or research becomes available during the trial that necessitates stopping.

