### Rationale for study

The most common treatments for PTSD are exposure therapy [23], eye movement desensitization and reprocessing (EMDR) [24], referral to support groups/interpersonal counseling [25, 26], and/or psychiatric medication or other medications to treat physical symptoms [27]. Although these strategies demonstrate some effectiveness in the general population with PTSD, they are unlikely to be fully effective for bereaved mothers for a variety of reasons. First, bereaved mothers’ engagement in treatment (e.g., initiation of therapy, support groups) is uncommon (<25%) [13]. Second, because bereaved mothers may be trying to conceive again, or have already conceived, they are often reluctant to take psychiatric medication, preferring non-pharmacologic alternatives [1]. In addition, medication cannot address the psychosocial aspects of grief and the accompanying emotional distress [28]. Third, though support groups for bereaved parents may provide a familiar and safe environment to connect with others who have had similar experiences [29, 30], these groups often have little to no emphasis on adaptive coping strategies for PTSD symptoms (e.g., hypervigilance, intrusion, avoidance) and the underlying emotional etiology [19, 31]. Fourth, bereaved mothers report unique barriers to participation in activities outside the home, such as encountering other babies in public, and many express strong interest in home-based treatments [32]. Finally, women may not have access to specialized treatment (e.g., exposure therapy, support groups) based on where they live, insurance coverage, or access to specialized clinicians, resulting in limited options for treatment [30, 33, 34]. It is crucial for science to develop novel approaches to inter-conception care amenable to the needs of these mothers.

Yoga may be an ideal treatment for addressing the unique PTSD symptoms of bereaved mothers after the death of a baby. Several studies have demonstrated that yoga is efficacious, safe, acceptable, and cost-effective for improving mental health in a variety of populations, including pregnant and postpartum women [35–41]. Yoga has also been used as a means to cope with PTSD symptoms after traumatic events (e.g., interpersonal violence, war, natural disasters) [42–45]. To date, there are no known studies examining yoga as a strategy to help bereaved mothers cope with PTSD symptoms after stillbirth.

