### Eligibility criteria

Inclusion and exclusion criteria for phase 1 (iterative design and interviews) are described in Table 1, and those for phase 2 are described in Table 2.

**Table 1 Tab1:** Phase 1 eligibility criteria

Inclusion
Iterative design
• Able to read/understand/speak English
• Women who experienced stillbirth within past 6 weeks to 24 months OR
• Women who have not experienced stillbirth but have given at least one live birth who regularly practice yoga (participate in yoga >60 min/week)
Interviews
• Able to read/understand/speak English
• Racial/ethnic minority women
• Women who experienced stillbirth within past 6 weeks to 24 months
• Not regularly practicing yoga (participating in yoga <60 min/week)
• Underactive (≤120 min/week moderate-intensity physical activity)
Exclusion
Iterative design
• Women who have experienced stillbirth that regularly practice yoga (i.e., ≥60 min/week)
• Pregnant women
• Unstable psychiatric condition (psychosis; suicidal ideation with plan)
Interviews
• Caucasian women
• Unstable psychiatric condition (psychosis; suicidal ideation with plan)

**Table 2 Tab2:** Phase 2 eligibility criteria

Inclusion
• Women who experienced stillbirth within past 6 weeks to 24 months
• Clinical levels posttraumatic stress symptoms (score of ≥33 on IES)
• ≥18 years of age
• Residing in the USA
• Able to read/understand/speak English
• Underactive (≤120 min/week moderate-intensity physical activity)
• Willing to be randomized
• Regular internet access via mobile phone, desktop/laptop computer, tablet, and etc.
• Answer “no” to all items on the PAR-Q (can participate safely)
Exclusion
• Unstable psychiatric condition (psychosis; suicidal ideation with plan)
• Pregnant at time of enrollment^a^
• Practicing yoga at least 60 min/week
• Unwilling to be randomized to a group
• Score of 20–27 of PHQ-9 (severe depression score)
• At risk for suicide based on follow-up phone assessment by [name] after positive screen (PHQ-9 score of 1, 2, or 3)

^a^Pregnant women will not be eligible for initial recruitment into the study. Women who become pregnant during the study will complete a PARmed-X for Pregnancy with their physician to identify any contraindications to yoga and will be able to continue participation

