### Data management

The research participant will self-report data electronically via Qualtrics. Weekly, the research team will be responsible for ensuring the completeness and timeliness of the data reported by the participants. Additionally, the research team will skim the data after each collection time point to ensure it is complete and will follow-up with any participants in which data collection is not complete.

Data quality will be monitored throughout the study. Measurement values will be compared to their known ranges. Out of range values will be investigated and either corrected if possible or treated as missing data. Statistical analyses will adjust for baseline demographic characteristics when statistically appropriate. Multiple imputations will be used to conduct statistical analysis with missing data. In the event that the missing at random assumption is violated, we will model the missing data mechanism and conduct sensitivity analysis on model parameters.

We have multiple strategies in place to identify yoga participation both during video sessions and outside of video sessions. First, we will be collecting 24-h, time-stamped GENEActiv accelerometer data at baseline, post-intervention (12 weeks), and follow-up (20 weeks) and will have a full record of their activity level during these time points. We will also be monitoring UDAYA website log-in information and will be able to localize activity monitor data while the participant is logged into the website and using the yoga videos. This will allow us to verify whether the participant is being active during the times they are using the website. Second, we will collect self-reported minutes of yoga using a log. This self-report log will also give us a time stamp of yoga activity that we will be able to cross-refer to the accelerometer data. Finally, we will be able to monitor all other physical activities that are performed outside of yoga, examining whether the intervention may have unintended effects of activity within other types of physical activity. Collectively, we will have a full record of yoga and physical activity (outside of yoga) participation that we will be able to use to understand the “dosage” that is being achieved for this trial.

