#### Missing data

Substantial missing data are anticipated in this study. Participants may refuse to participate or withdraw from the study at any time. In addition, daily and weekly logs may not be complete despite efforts by research staff to encourage completion. Missing data due to non-response on certain items within a scale will initially be handled by creating an average scale score for all participants who responded to at least 75% of items on that scale. We will evaluate whether missingness due to attrition is related to group membership and examine relations between missingness and any missing individual’s pretest scores on outcome variables. If missingness is found to satisfy the missing at random assumption, we will handle the missing data using multiple imputation. Multiple imputation will also be used to handle item-level missingness for final analyses of scales. In the event that the missing at random assumption is violated, we will model the missing data mechanism and conduct sensitivity analysis on model parameters. All analyses will retain all participants who were assigned to the intervention or control groups (i.e., intent to treat).

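### The rule on outside practice covers only face-to-face classes, so uptake of non-study online, app-based or home yoga after randomization is not discouraged in any arm

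*Protocol article*

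**What the plan says.** The Procedures section for phase 2 contains one rule on practice outside the study: "Participants will be discouraged from attending face-to-face yoga/stretching/toning classes during the study". No other section asks women to refrain from non-study yoga online, through an app or at home.

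The same section limits each account on the study platform to the videos of the woman's own arm: "participants will not have access to the full UDAYA video library". The control prescription is also delivered online: "The STC group will be asked to follow a 12-week online stretching/toning exercise prescription for 60 min/week".

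The Rationale for study says that these mothers report barriers to activities outside the home and that "many express strong interest in home-based treatments". Table 2 requires regular internet access and lists as an exclusion "Practicing yoga at least 60 min/week". That is an entry criterion, and nothing in the article turns it into a limit after randomization. On the low dose the article says: "We selected the low dose of 60 min/week because this is the minimal amount needed to experience mental and/or physical health benefits".

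Outside practice is to be recorded. Under Data management: "We have multiple strategies in place to identify yoga participation both during video sessions and outside of video sessions". The Missing data section commits all analyses to intent to treat.

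**The concern.** The sponsor evidently thought contamination worth controlling, because it wrote the rule and restricted accounts by arm. But the rule targets classes attended in person, which the article's own rationale makes the less likely route for these women. They are recruited largely through web channels and all have internet access. A control woman who starts yoga on another website breaches no stated rule. Nor does a low-dose woman who adds outside sessions.

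Two things depend on the arms differing in yoga received. One is objective 3, the preliminary effect on PTSD symptoms. The other is the decision described under Sample size: if both yoga arms do better than control, the low-versus-moderate comparison determines whether the feasibility data are used to choose between doses. Under intent to treat, yoga taken up by controls stays in the contrast and pulls it towards zero.

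**Working it through.** **Inputs from the article.** From Sample size: 90 enrolled, 20% attrition, 72 retained, Cohen's d = 0.80 for one yoga arm against control, p < 0.05, power 0.80. Allocation is equal across three arms. A two-sided test is assumed because the article does not state sidedness.

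**The plan's own figure.** 90 × 0.8 = 72, and 72 / 3 = 24 per arm. The noncentrality is d × √(n/2) = 0.80 × √12 = 2.77.
- Normal approximation: Φ(2.77 − 1.96) = Φ(0.81) = 0.79.
- Two-sided t test with 46 degrees of freedom: 0.774.

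The stated 0.80 is reproduced approximately. There is no reserve for dilution.

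**Inputs the article does not give (assumptions).** c is the share of controls who take up outside yoga, set at 10% to 30%. s is the share of the yoga effect such a woman gains, set at one half or all of it. Outside yoga in the yoga arms is taken to add nothing.

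**Formula.** Diluted contrast = 0.80 × (1 − c × s). Power is from the two-sided t test with 24 per arm.

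| c | s | Contrast d | Power |
|---|---|---|---|
| 0 | – | 0.80 | 0.77 |
| 10% | 0.5 | 0.80 × 0.95 = 0.76 | 0.73 |
| 20% | 0.5 | 0.80 × 0.90 = 0.72 | 0.69 |
| 30% | 0.5 | 0.80 × 0.85 = 0.68 | 0.64 |
| 10% | 1 | 0.80 × 0.90 = 0.72 | 0.69 |
| 20% | 1 | 0.80 × 0.80 = 0.64 | 0.58 |
| 30% | 1 | 0.80 × 0.70 = 0.56 | 0.48 |

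**Low versus moderate dose.** The prescribed gap is 150 − 60 = 90 min/week. Each outside minute added by a low-dose woman narrows it. The article states no effect size for this comparison, so no power figure is attempted.

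**What the monitoring can see.** The accelerometer is worn for one week at baseline, 12 weeks and 20 weeks. Under Study enrollment, log-in details follow the baseline wear week, so the accelerometer covers little or none of the intervention itself. Platform tracking cannot see other websites. For most of the 12 weeks, outside yoga is therefore known only from self-report, and the Missing data section expects daily and weekly logs to be incomplete.

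**The case against.** Several points on the other side have force.

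- **Partial containment.** Restricting accounts by arm closes the most obvious source, and weekly and daily logs already ask about other activity and yoga sessions. This stands. But recording outside yoga neither prevents it nor removes it from an intent-to-treat contrast.
- **Exploratory aim.** Sample size says that aim 3 is not meant to be fully powered, and seeing how much yoga controls take up is useful in itself for planning the full trial. This stands too. It limits the harm to preliminary estimates, but those estimates are what the full trial would be planned on.
- **Condensed article.** The participants' packets may say more. That is possible, but the article does state the rule and states it for one setting only.

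Two stronger readings are tempting. A reader might infer that the entry criterion, which admits women doing up to 59 min/week of yoga, already lets controls receive almost the low dose. The article does not support this. Prior practice is allowed in every arm and balanced in expectation by randomization, so if effects add, stable practice does not shrink the contrast. Moreover, 59 minutes lies below the amount that the article itself calls minimal for benefit. The issue is uptake after randomization.

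A reader might also infer that contamination would make the control look falsely suitable under objective 2. It would not: that objective and its benchmarks judge the control on adherence and satisfaction, and outside yoga counts towards neither.

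**Conclusion.** The point holds as a gap in the scope of one stated rule. Uptake of non-study online, app-based or home yoga is discouraged in no arm, although the article's own description of these women makes that the likelier route. The contrasts at risk are yoga versus control and low versus moderate dose, both exploratory.

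The size is conditional. For 10% to 30% uptake among controls and half to all of the effect gained, d falls from 0.80 to between 0.76 and 0.56, and power from 0.77 to between 0.73 and 0.48. The lower end is a worst case. If the yoga arms took up outside yoga to the same extent and effects added, the yoga-versus-control contrast would not shrink. The figures show sensitivity and do not forecast what will happen. The change is worth making because it is cheap, not because serious bias has been shown.

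**What to change.** In Procedures, extend the discouragement to any non-study yoga or stretching/toning practice, whether face-to-face, online, app-based or at home, and limit this wider wording to the 12-week intervention period. The limit matters. The study runs to week 20, and the feasibility measures count intent to continue and continued use of skills as favourable, so a ban through follow-up would conflict with them.

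Put the same sentence in the packets and weekly reminders of all three arms. Report outside-yoga minutes by arm from the logs already collected, so that the separation achieved can be read beside the effect estimates.

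The cost is one sentence in the protocol, packets and reminders, and one table. The downside is that some women may under-report outside yoga once it is discouraged, which would weaken the dosage record somewhat.

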**Fig. 1 Fig1:**
[figure not shown]
Study flow chart: the *left side* of the diagram illustrates the flow of the study for phase 1, and the *right side* illustrates the phase 2

#### Phase 1

Part A. Iterative design: We will develop the yoga prescription using an iterative design process with the following steps:Identify 30 videos from the existing UDAYA (an online-streaming commercial yoga website; https://udaya.com) library.Gather a panel of women whose babies were stillborn (*n* = 5) and a panel of women who are regular yoga practitioners and have not experienced a baby’s death (*n* = 5) to review (i.e., watch or engage) yoga videos selected from step one above.Develop (produced by Udaya.com) up to 12, 30-min yoga videos specifically for the grieving mothers.

Part B. Interviews to identify cultural barriers to recruitment: We will recruit five non-Caucasian (predominately Hispanic and/or African American) women who have experienced stillbirth to participate in a 15–20 min phone interview. These interviews will guide the recruitment process for phase 2, and additional recruitment materials will be developed to ensure adequate enrollment of non-Caucasian women in the study. The interview questions will consist of questions related to:Perceptions/opinions about yoga related to physical and mental health.Strategies to ensure adequate enrollment and retention of non-Caucasian women to participate in a yoga intervention.

#### Phase 2

Phase 2 is a three-group randomized feasibility trial with assessments at baseline and at 12 and 20 weeks from baseline. After completion of the consent process and the baseline assessment, 90 women will be randomized into one of the following three arms for 12 weeks: (1) intervention low dose (LD) = 60 min/week yoga (*n* = 30), (2) intervention moderate dose (MD) = 150 min/week yoga (*n* = 30), or (3) stretch and tone control (STC) group = 60 min/week of stretching/toning exercises (*n* = 30).

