### Sample size

We aim to enroll 90 participants. Assuming an attrition rate of 20%, we will have a final sample of 72 women with data through a 20-week follow-up. This sample size is appropriate for early-phase developmental trials [60]. While we do not intend to fully power our exploratory aim 3, we do anticipate sufficient power to detect a large effect (to detect a large effect of Cohen’s *d* = .80) between a treatment arm and control group on primary (PTSD symptoms) and secondary (anxiety, depression, self-compassion, emotional regulation, sleep disturbance) outcomes with *n* = 72 (*p* < 0.05, power = 0.80). The power of the study is such that large effects will be detectable and the directionality of effects will be sufficiently stable to assess the preliminary merit of the intervention and provide information needed for future larger studies. Effect sizes will be calculated along with tests of significance. Effects of intervention on physical activity, mindfulness, and perceived exertion will be explored using mixed models or multilevel models to examine multiple waves of data from weekly logs and GENEActiv. Effects of intervention should emerge as significant regression coefficients for the group membership predictor in accounting for within-person intercepts and slopes. Planned contrasts will compare three groups (LD, MD, and control) for differing trajectories over time. If both yoga groups show greater improvements on outcomes than the control group and there are significant differences between LD and MD, this would indicate that one group may lead to improved outcomes. If both yoga groups improved more than the control group, and there are *no* significant differences between LD and MD, we will use feasibility data to determine which group is more feasible.

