### Allocation (phase 2 only)

Block randomization will be used to assign participants to treatment groups. Specifically, the biostatistician will construct 15 blocks of six participants using SAS PROC PLAN with a random number seed known only by the biostatistician. This will be done at the beginning of the study (front-loaded) and provided to a research staff member not associated with this study (i.e., trusted broker). The trusted broker will utilize the treatment allocations to sequentially assign enrollees to randomized treatment groups (the biostatistician will be shielded from enrollment date and enrollment order, and participant IDs will not reflect enrollment order). The trusted broker will hold the codes that match participants to treatment groups. Research staff members will call the trusted broker to determine assignment to group. In case of adverse events (AE), the research staff member will call the trusted broker to provide for unblinding (AE only). After randomization, participants will be emailed a study information packet (i.e., instructions, UDAYA username/password) according to the intervention assigned. The initiation of the study will begin after allocation to study arm (see Fig. 2 for phase 2 study flow chart).

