At 6 weeks (midway through the intervention), participants will be asked to complete the IES-R and answer a 1-item Likert-based question related to whether they think the intervention is contributing to their symptoms for the IMC to review. Every 2 weeks of the intervention, participants will be asked to fill out the PHQ-9 via Qualtrics within 48 h. A research team member will monitor PHQ-9 completion daily (including weekend/holidays). Women with scores suggestive of clinical depression (>15) will be notified and advised to follow up with their primary care physician. If suicidal ideation is noted with a screen score of two or three on question 9 of the PHQ-9, the participant will be contacted within 24 h by a crisis-trained, clinical staff for further assessment of risk. Clinical providers trained by the MISS Foundation are well equipped to handle psychological crises, have a system currently used for their existing 3000 grieving families they help annually, and have staff available on weekends/holidays. If imminent suicidal risk is present, the staff will follow MISS Foundation emergency procedures to ensure participant safety, and the participant will be discontinued from the study. If there are no concerns for active suicidal risk after the phone assessment, the participant will be able to continue in the study if she desires. All participants will have the MISS Foundation provider’s phone number, and the research personnel can either email, call, text, or page the lead clinical provider to respond to psychiatric issues. Depending on the need of the participant, one of them will be able to talk to a clinician within 2 to 3 h.

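### The only numeric stopping criterion for harm pools the three arms, so beyond the first three women enrolled it cannot be met by deterioration confined to one arm

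*Protocol article*

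**What the plan says.** The Procedures section (Interventions, Phase 2) lists three grounds for stopping the study early. The first is clinical deterioration of PTSD symptoms, defined as "increased scores of >20 points from baseline on the Impact of Event Scale-Revised (IES-R) in >50% of the enrolled participants". The second concerns recruitment. The third allows a stop if new safety information or research calls for it, with no number attached.

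Under Study design, Phase 2, "90 women will be randomized into one of the following three arms for 12 weeks". These are low-dose yoga, moderate-dose yoga and control, with 30 women each; the last is the "stretch and tone control (STC) group = 60 min/week of stretching/toning exercises (*n* = 30"). Under Allocation, "the biostatistician will construct 15 blocks of six participants". Under Sample size, "Assuming an attrition rate of 20%, we will have a final sample of 72 women".

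Three other places bear on how harm is seen:
- **Adverse events.** The Independent Monitoring Committee (IMC) receives counts and rates of non-serious events for each group. The same section says: "At 6 weeks (midway through the intervention), participants will be asked to complete the IES-R". That is for IMC review, with an item on whether the woman thinks the intervention contributes to her symptoms. The PHQ-9 is repeated every two weeks, with action limits for the individual woman.
- **Reporting.** Tables in the study reports for the IMC use pooled baseline and safety data only, not split by arm.
- **Blinding.** The principal investigator and biostatistician stay blinded until data lock. The study coordinator and graduate student worker, who prepare the IMC reports, are unblinded.

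**The concern.** The criterion is a share of all enrolled women, and each arm is one third of them. A limit above one half therefore lies beyond what one arm can contribute, however badly its participants fare. The trial compares two amounts of yoga with a control programme in women who enter with clinical-level PTSD symptoms, so worsening in one arm is a plausible event to monitor. The stated criterion would not register it, and if the Reporting section governs, the IMC's tables would not show it either. At stake is whether a one-arm signal on the trial's main symptom scale reaches the people charged with acting on it.

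**Working it through.** **Inputs.** Limit: more than 50% of enrolled women, each with an IES-R rise of more than 20 points (Procedures). Total 90, three arms of 30 (Study design, Phase 2). Fifteen blocks of six (Allocation); two per arm in each block is inferred from the 30:30:30 split. Attrition 20% (Sample size). I take enrolled to mean randomized.

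**The plan's own totals reproduce.** 3 × 30 = 90; 15 × 6 = 90; 90 × 0.80 = 72, or 24 per arm if losses are even.

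**Women needed to exceed the limit.** The smallest whole number above N/2 is 46 for N = 90 and 37 for N = 72.

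**Harm in one arm only.**
- Largest share: 30/90 = 33.3%. With even attrition: 24/72 = 33.3%.
- Shortfall at 90: 46 − 30 = 16, so 16 of the other 60 women (26.7%) must also deteriorate.
- Shortfall at 72: 37 − 24 = 13 of the other 48 (27.1%).

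**One arm entirely deteriorated, with background deterioration elsewhere.** The background rates are assumptions; the protocol gives none. The expected pooled share is (30 + 60p)/90. The probability of meeting the criterion is the binomial chance of at least 16 of 60 at rate p.

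| Background rate p | Expected pooled share | Probability criterion is met |
|---|---|---|
| 0% | 33.3% | 0 |
| 10% | 40.0% | 0.0002 |
| 20% | 46.7% | 0.13 |
| 25% | 50.0% | 0.43 |
| 30% | 53.3% | 0.76 |

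**Harm in both yoga arms, none in control.** 45 of 60 (75%) gives 45/90 = 50.0%, which equals but does not exceed the limit. 46 of 60 (76.7%) is needed. If the true rate in the yoga arms were 70%, the probability of at least 46 of 60 is 0.16; at 80% it is 0.79.

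**During accrual.** With two per arm in each block of six, the largest possible number in one arm after n women is 2 × (complete blocks) + min(2, remainder).
- n = 1, 2, 3: 1/1, 2/2, 2/3, all above 50%.
- n = 4 and n = 8: 2/4 and 4/8, exactly 50%, not exceeded.
- Every other n up to 90: below 50%.

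The exception is therefore the first three women. The first scheduled post-baseline IES-R is at week 6. At an even pace over the eight recruitment months in the timeline (90/8, about 11 a month), more than three would be enrolled by then.

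**If the denominator were women with IES-R data.** With one arm of 30 fully observed, 30/59 = 50.8% exceeds the limit and 30/60 = 50.0% does not. At most 29 of the other 60 could be observed, so at least 31 (51.7%) must be missing, against a planned 20%.

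**The case against.** The strongest reply is that this rule is not the trial's only protection. Serious events get expedited review, and the IMC also meets ad hoc when adverse events occur. It reviews the week-6 IES-R, non-serious event rates are to reach it by group, and the PHQ-9 triggers action for individual women. The third stopping ground is broad enough to cover an imbalance between arms. This is a feasibility trial, and a pooled rule helps to preserve blinding. The ethics section also mentions approved data and safety monitoring plans that are not shown and may describe arm-level review.

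Much of this stands. A reader might infer that harm in one arm would go unmonitored, or that the study could not be stopped for it. The document does not support that: there are routes by which such harm could come to light, and a discretionary ground for acting. What these safeguards do not supply is an arm-level criterion for IES-R deterioration, and the Adverse events and Reporting sections disagree on whether the IMC sees safety data by arm at all.

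A reader might also infer that the rule is faulty because it could stop the study when all arms worsen alike. That does not follow. The control is itself a programme delivered by the study, and a stop when most participants deteriorate protects them whatever the cause. It is a reason to keep the pooled criterion.

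**Conclusion.** The point holds in a narrow form. As written, the only numeric harm criterion cannot be met by deterioration confined to one arm once more than three women are enrolled: the ceiling is 33.3% against a limit above 50%. Harm confined to both yoga arms must reach 77% of those women. This rests on equal allocation, two women per arm in each block, and a denominator of enrolled women. Counting only assessed women would not change the conclusion at anything near the planned attrition, although early counts of assessed women need not follow the block balance, so the small-number exception could be somewhat wider. The probabilities in the table depend on assumed background rates; the ceiling does not. The criterion should be revisited, but the remaining safeguards limit the practical consequence.

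**What to change.** Reconcile the Procedures, Adverse events and Reporting sections on whether harm is judged by arm, pooled, or both. Keep the pooled criterion. Have the staff who are already unblinded and prepare the IMC reports add, for each arm, the number of women assessed and the number with an IES-R rise of more than 20 points. This should go in a report closed to the blinded principal investigator and biostatistician. The sponsor and the IMC should decide, and the protocol should record, whether any arm-level limit applies, its value, the minimum number assessed before it is read, and whether meeting it would halt an arm or the whole trial.

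The cost is two counts per arm in each IMC report and edits to three sections rather than one, because the Adverse events and Reporting texts must change with the stopping rule. The main drawback is that early arm-level percentages rest on few women, so each should be shown with its denominator.
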